**Study Population**

The study population will be drawn from the entire CPRD population with acceptable up to standard (UTS) follow up time. People will be selected for inclusion if they have received any prescription for a GTZ antidiabetic (code list in Appendix 1), with the first occurrence being at least 12 months after the patient’s start of UTS follow up. This is to increase the likelihood that we are studying new users of GTZs, which will be of importance when we assess any effect of treatment duration on PD risk. Eligibility will begin in 1999 when the first GTZ was launched. No age restrictions will be applied to eligibility; the mean age of type 2 diabetes diagnosis in a US population was ~ 46 years in 2000 (Koopman et al, 2005) and so we anticipate the age profile of patients receiving GTZ antidiabetics will be a little younger than the typical onset age for PD (over 50 year), making them an ideal group in which to study the long term effects of a potentially neuroprotective agent. Potential participants with any diagnosis of PD prior to their first GTZ prescription will be excluded. Users will be classified according to their diabetes treatment stage at the time the GTZ is started, as follows:

1. GTZ monotherapy, no prior oral anti-diabetic (OAD)
2. GTZ monotherapy, previous OAD discontinued
3. Combined OAD therapy, GTZ being taken with other OADs

A feasibility count shows there are ~43,000 incident GTZ users with at least 12 months prior UTS follow up. Follow up for the study analysis will begin at the first prescription for a GTZ and end at the earliest of last collection date for the practice, patient transfer out or death date.

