**Selection of Comparison Group**

Each GTZ exposed patient will be matched by age, sex, and practice with up to 5 patients receiving other oral treatment for diabetes (unexposed group). To reduce the possibility of confounding, we will only select patients who have also received oral antidiabetic treatments, thus reducing the difference in disease stage between GTZ users and non-users. GTZ prescribing has evolved during >10 years according to changes in treatment guidance and changes made to the licensed indication. Initially they were mostly used as second line combination treatment, but were subsequently also used at earlier stages of diabetes treatment. Rosiglitazone was eventually suspended due to cardiovascular safety concerns and pioglitazone use has waned due to concerns over the risk of bladder cancer. To be considered for inclusion, only patients present in the database from 1999 onwards and with at least 12 months UTS follow up prior to prescribing events that trigger eligibility will be included. For instance a patient could be matched to a GTZ user in category 1) above if they had never received an OAD before 1999 and began taking a sulphonylurea with no other OAD after at least 12 months UTS follow up. Follow up for the unexposed will begin at the first prescribing event that makes them eligible for inclusion.

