**Statistical Analysis**

We will measure an incidence rate ratio for the association between GTZ use and incident PD using poisson regression, comparing patients exposed to GTZs with patients exposed to alternative treatments. The primary analysis will follow all patients from their index date until the earliest of a PD record, transfer out/death, or last collection date for the practice, and their exposure will remain as defined at the index date, regardless of any subsequent changes in therapy (analogous to an intention to treat analysis in a clinical trial). Secondary analyses will be as follows:

- Censoring follow up at end of GTZ therapy, defined as last prescription plus 90 days, followed by at least 180 days GTZ-free follow up time.
- Stratified analysis based on metformin and GTZ treatment status, to explore the individual and any additive effects of both treatments. Whilst we anticipate most patients will be exposed to metformin, we anticipate a sizeable population who will not receive metformin.
- We have chosen to measure the incidence of PD from the start of therapy with GTZs as the pre-clinical work to date suggests a fast onset of any protective effect. Whether this effect varies with exposure length will be assessed through a stratified analysis on length of follow up after starting GTZ therapy.
- Sensitivity analysis defining PD as a Readcode indicating PD plus at least 2 prescriptions for an anti-Parkinson’s drug, to reduce the likelihood of outcome misclassification. Although cases with little follow up beyond their diagnosis will be excluded, this approach will only reduce study power, but will reduce misclassification bias. The date of earliest recorded diagnosis will remain the date of the outcome.
- Sensitivity analysis to look separately at the effects of pioglitazone and rosiglitazone.
- Sensitivity analysis adjusting for all variables identified as potential confounders, in addition to those included in the forward stepwise modelling strategy (see below).

Adjustments for potential confounding will be made in a forward stepwise manner retaining variables in the model if they have a substantial impact on the estimated rate ratio (a change of 10% or more), and starting with variables that have the greatest effect on PD incidence in univariate analyses. All data management and analyses will be performed using Stata 12 (StataCorp, Texas).

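### The secondary analysis meant to show variation with exposure length stratifies on follow-up since the first glitazone prescription, so it measures time since initiation, not duration of treatment

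*Protocol*

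**What the plan says.** The Statistical Analysis section gives the rule in one sentence: "Whether this effect varies with exposure length will be assessed through a stratified analysis on length of follow up after starting GTZ therapy". The Study Population section shows that treatment duration is the intended question. It requires the first GTZ prescription to fall at least 12 months after the start of up-to-standard follow-up, so that new users are studied, "which will be of importance when we assess any effect of treatment duration on PD risk".

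Follow-up is defined in two places. In Study Population it is to "end at the earliest of last collection date for the practice, patient transfer out or death date". In the primary analysis it runs "until the earliest of a PD record, transfer out/death, or last collection date for the practice". Stopping the GTZ ends it in neither place, and exposure is kept as assigned at the index date "regardless of any subsequent changes in therapy (analogous to an intention to treat analysis in a clinical trial").

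A separate secondary analysis does stop at the end of treatment: "Censoring follow up at end of GTZ therapy, defined as last prescription plus 90 days", followed by at least 180 GTZ-free days. It is not divided by duration, and nothing links it to the exposure-length analysis. No listed analysis uses cumulative time on GTZ or number of prescriptions.

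Selection of Comparison Group states: "Rosiglitazone was eventually suspended due to cardiovascular safety concerns and pioglitazone use has waned due to concerns over the risk of bladder cancer".

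**The concern.** The sentence that sets the analysis names one variable as the question (exposure length) and another as the stratifier (length of follow-up). The two agree only while patients stay on the drug. A patient with a single GTZ prescription and ten years of follow-up contributes to the longest band, although almost all of that time is unexposed.

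This is not a detail left to a later analysis plan, because the protocol has already chosen the variable. What is at stake is how the band-specific results will be read. A rate ratio moving towards 1 in later bands could be taken as protection wearing off with longer treatment, when it might only reflect patients having stopped. The Background section says the results should inform where further clinical research is directed, so that misreading would matter.

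**Working it through.** **The plan's own figure.** The only computed figure is the power. Inputs from Power Calculation: 43,000 exposed, 144 PD cases among them, five unexposed per exposed (5 × 43,000 = 215,000). Exposed risk is 144/43,000 = 0.00335. Unexposed risk for a reduction r is 0.00335/(1 − r): 0.00478, 0.00447 and 0.00419 for 30%, 25% and 20%. A two-sample comparison of proportions at two-sided 5% (the level is assumed; it is not stated) gives 99.0%, 92.0% and 71.8%, or 98.9%, 91.3% and 70.3% with a continuity correction. The protocol states 99%, 91% and 71%. These reproduce, and they concern the overall comparison, so this point does not touch them.

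**What a follow-up band estimates.** Let s be the share of exposed person-time in a band that is still on drug, 0.75 the on-drug rate ratio (the 25% reduction the protocol calls clinically meaningful), and c the fraction of the effect that persists after stopping. Then approximately

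band RR = s × 0.75 + (1 − s) × (1 − 0.25c) = 1 − 0.25 × [s + c(1 − s)].

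The shares s and the values of c are assumptions.

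| Share on drug | c = 0 | c = 0.5 | c = 1 |
|---|---|---|---|
| 100% | 0.75 | 0.75 | 0.75 |
| 70% | 0.825 | 0.79 | 0.75 |
| 40% | 0.90 | 0.825 | 0.75 |
| 20% | 0.95 | 0.85 | 0.75 |

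The on-drug effect is the same in every row. Any trend down a column comes from discontinuation alone.

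**A growing effect can also seem to fade.** Assume on-drug rate ratios of 0.75, 0.70, 0.65 and 0.60, the same shares and c = 0. The band values are 0.75, 1 − 0.30 × 0.7 = 0.79, 1 − 0.35 × 0.4 = 0.86 and 1 − 0.40 × 0.2 = 0.92.

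**Simulation check.** Four million patients per group; constant on-drug RR 0.75 and RR 1 off drug. Further assumptions, none from the documents: PD rate 0.8 per 1,000 person-years, potential follow-up uniform from 0.5 to 12 years with other exits, exponential time on drug with mean 2, 3 or 5 years. Ranges run across the three means.

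| Years since start | Off-drug share | RR, all follow-up | RR, on-drug time only |
|---|---|---|---|
| 0–2 | 17–36% | 0.77–0.85 | 0.73–0.76 |
| 2–5 | 48–80% | 0.90–0.95 | 0.75–0.77 |
| 5–12 | 75–96% | 0.98–1.01 | 0.77–0.79 |

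Restricting to on-drug time recovers the constant 0.75 to within simulation noise; the planned stratifier does not.

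**Does ending follow-up at PD add bias?** With person-time split into bands, the null simulation gives rate ratios of 1.00–1.02, so it does not. If patients are instead grouped by total follow-up, the rates are distorted (about 6.0, 1.4 and 0.3 per 1,000 under the null), but the ratio stays near 1 when comparators are grouped the same way. Only grouped users set against all unexposed patients (0.8 per 1,000) would give spurious ratios, of about 7.5, 1.7 and 0.4.

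**The case against.** The best defence is that the planned analysis answers a question the protocol does ask. Study Design says the cohort will allow the authors to examine whether any effect changes over time, and the bullet itself opens with the expected speed of onset. Time since initiation suits both. An on-treatment analysis is also listed, and time bands within it would largely track time on drug. This stands as far as it goes: the analysis is valid for time since start, and the defect is its label and the missing link to on-treatment time. It does not answer the treatment-duration aim in Study Population.

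A second defence is biological. The hypothesis is neuroprotection, so benefit may persist after stopping, and with full persistence no fading appears. That is correct, which is why the size is given as a range. The planned analysis cannot, however, separate persistence from duration.

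A reader might also infer more than the documents support:

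- **That the strata are biased because PD ends follow-up.** This needs grouping by total follow-up, and serious distortion of the rate ratio also needs an ungrouped comparator. The protocol states neither. Splitting person-time is usual with Poisson regression and removes the problem.
- **That late follow-up is mostly off drug.** The protocol reports suspension and declining use but gives no dates, persistence or treatment lengths. Some off-drug time must be expected; how much is unknown.
- **That duration-response is the plan's main causal evidence.** The sole objective is the overall rate ratio, and this is one of six secondary or sensitivity analyses.

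**Conclusion.** The concern holds in a limited form. The analysis assigned to exposure length uses a variable that keeps accruing after treatment stops, so it measures time since initiation. No other listed analysis covers duration of treatment.

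The consequence depends on how many patients stop and how far protection persists. In the illustration, a constant on-drug rate ratio of 0.75 appears as 0.95 in the last band with no carry-over, 0.85 with half carry-over, and 0.75 with full carry-over. Neither discontinuation nor carry-over can be estimated from the documents, so the mismatch is certain while its size is not. The primary rate ratio and the stated power are unaffected. The change should be made, but it concerns a secondary analysis only.

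**What to change.** 1. Relabel the planned analysis as effect by time since initiation, and state that person-time is split into bands from the index date in both groups.
2. For exposure length, add time-updated cumulative GTZ exposure built from prescription records, with each person-year classified only by past prescriptions. Fix the categories before results are seen. At minimum, apply the time bands within the on-treatment censoring already planned.

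The prescription dates are already needed for that censoring, so the direct cost is some data management. Two downsides should be acknowledged.

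- **Few events.** There are 144 exposed cases in all. If they fell equally into three categories (48 each, an assumption) and each was compared with all unexposed cases (5 × 144/0.75 = 960, assuming equal follow-up per patient), the standard error of the log rate ratio would be √(1/48 + 1/960) = 0.148. An estimate of 0.75 would then carry a 95% interval of about 0.56 to 1.00.
- **Selection by persistence.** Patients who stay on a GTZ may differ from those who stop, so a trend across cumulative exposure is not by itself evidence of a causal duration effect. The interpretation should say so.

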**Patient or User Group Involvement**

We do not believe this research would benefit from patient or user group involvement at the current stage, but may be more relevant at the time of dissemination or consideration of further related research.

**Limitations of the Study Design, Data Sources and Analytic Methods**

Diagnoses of PD in the CPRD have a positive predictive value of 90% (Becker et al, 2008) and so a small degree of misclassification amongst outcomes is expected. However, this is likely to be non-differential with respect to GTZ exposure and would be expected to bias results towards the null. In addition, missing cases of PD are likely to be rare in our study population, given that the prevalence of PD is low in the general population. Misclassification of the exposure is also likely to occur to some degree, with patients not being completely adherent to prescribed medicines. However, diabetes is a serious condition for which patients are likely to be motivated to take their medication, and substantial misclassification is not anticipated. Again, misclassification is unlikely to be differential with respect to PD status and so a dilution of any effect towards the null would be expected.

Whilst a small number of risk factors for PD are known and will be accounted for in the design and analysis (e.g. age, sex, smoking), it is not anticipated that these factors will be strongly associated with the choice to prescribe a GTZ, and so confounding is not expected to be strong in this study. Nonetheless, the analysis plan ensures potential confounding will be addressed, and in particular the separate and potentially additive effects of GTZs and metformin will be assessed.

Since the study is conducted entirely within the population with diabetes, the generalisability of results may be affected. However, it is unlikely that any pharmacological effect of GTZs relevant to PD would be limited to people with diabetes only.

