**Power Calculation**

Amongst the 43,000 GTZ exposed patients identified for the feasibility count, 144 were first diagnosed with PD after starting a GTZ. Using STATA 12, we estimate we will have 99% power to detect a 30% reduction in PD incidence amongst GTZ users, if we match each exposed patient to five unexposed. Power to detect a 25% and 20% reduction will be and 91% and 71% respectively. We believe an effect size of 25% would represent a clinically meaningful association, and may also be plausible, given the near complete protection identified in animal studies (Sadeghian et al, 2012).

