**Appendix 2: Codes used to identify Parkinson’s Disease**

Parkinson’s disease with no identified cause

| medcode | readterm |
| --- | --- |
| 1691 | paralysis agitans |
| 4321 | parkinson's disease |
| 8956 | parkinsonism with orthostatic hypotension |
| 9509 | [x]dementia in parkinson's disease |
| 10718 | o/e - parkinsonian tremor |
| 14912 | parkinson's disease nos |
| 16860 | o/e - parkinson gait |
| 17004 | o/e - parkinson posture |
| 53655 | o/e -parkinson flexion posture |
| 59824 | o/e-festination-parkinson gait |
| 86062 | [x]parkinsonism in diseases classified elsewhere |
| 96860 | cerebral degeneration in parkinson's disease |

Parkinsonism with identified causes

| medcode | readterm |
| --- | --- |
| 19478 | drug induced parkinsonism |
| 24001 | secondary parkinsonism due to other external agents |
| 26181 | secondary parkinsonism, unspecified |
| 33544 | parkinsonism secondary to drugs |
| 51105 | postencephalitic parkinsonism |
| 52589 | syphilitic parkinsonism |
| 72879 | [x]secondary parkinsonism, unspecified |
| 97170 | [x]other secondary parkinsonism |
| 100128 | vascular parkinsonism |

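### The covariate list has no cardiovascular or cerebrovascular history, so a possible small bias from uncoded vascular parkinsonism cannot be adjusted for

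*Protocol*

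**What the plan says.** **Confounding.** The Limitations section names age, sex and smoking as examples of known PD risk factors, and continues that "it is not anticipated that these factors will be strongly associated with the choice to prescribe a GTZ". It concludes that confounding should not be strong.

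**Outcome error.** The same section takes a positive predictive value (PPV) of 90% for PD records from a cited study. It says of the error that "this is likely to be non-differential with respect to GTZ exposure" and expects the bias to be towards the null.

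**Prescribing history.** Selection of Comparison Group says that glitazone use changed with guidance and licensing, and adds: "Rosiglitazone was eventually suspended due to cardiovascular safety concerns and pioglitazone use has waned due to concerns over the risk of bladder cancer".

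**Covariates.** Exposures, Outcomes and Covariates lists smoking, HRT, head trauma, age and sex, calcium channel blockers, diabetes duration, HbA1c, metformin, alcohol, body mass index and calendar year. Stroke, ischaemic heart disease, heart failure and hypertension are absent.

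**Outcome definition.** Appendix 2 puts "vascular parkinsonism" among the parkinsonism codes with an identified cause. Exclusion depends on such a code being recorded.

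**Analysis.** Statistical Analysis keeps a covariate if it moves the rate ratio by at least 10%. Sensitivity analyses adjust for all identified potential confounders, require at least two anti-Parkinson's prescriptions, and take pioglitazone and rosiglitazone separately.

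**The concern.** A patient whose parkinsonism is vascular, but who has only a general PD code, counts as a PD case. If vascular disease also influenced who was started on a glitazone, such false cases would be unevenly spread between the groups. Were they fewer among glitazone users, the rate ratio would fall below 1 with no drug effect. That is the direction of the study hypothesis, and it departs from the bias towards the null that the Limitations section leads readers to expect.

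The fully adjusted sensitivity analysis draws on the same covariate list, so it cannot correct for a history that is not collected. The Protocol fixes this list itself, so the gap is not a detail left for a later document.

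**Working it through.** **1. The Protocol's own figures.** Inputs: "A feasibility count shows there are ~43,000 incident GTZ users with at least 12 months prior UTS follow up" (Study Population); "144 were first diagnosed with PD after starting a GTZ" (Power Calculation); up to five comparators per exposed patient (Selection of Comparison Group). The Protocol states "99% power to detect a 30% reduction in PD incidence amongst GTZ users", with 91% and 71% for reductions of 25% and 20%. Take 144/43,000 as the risk in glitazone users, 144/43,000 divided by the rate ratio as the comparator risk, 1:5 allocation and a two-sided 5% test (the test level is assumed, as none is stated). A two-proportion calculation then gives 99.0%, 92.0% and 71.8%. With a continuity correction it gives 98.9%, 91.3% and 70.3%. The stated power reproduces, so no stated figure is wrong. The event counts can be used below.

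**2. Bias model.** Suppose there is no true effect. Let f be the share of comparator PD records that are false, and k the rate of false records in glitazone users relative to comparators. Then

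observed rate ratio = (1 − f) + f × k.

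The 90% PPV gives f = 0.10. No document gives k, so it is varied:

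| k | Observed rate ratio |
|---|---|
| 0.75 | 0.90 + 0.075 = 0.975 |
| 0.50 | 0.90 + 0.050 = 0.95 |
| 0 (floor) | 0.90 |

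**3. What k requires.** Let vascular disease multiply the false-record rate by R, with prevalence a in glitazone users and b in comparators. Then k = (1 + a(R − 1)) / (1 + b(R − 1)). All three inputs are assumptions.

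- R = 2, b = 30%, a = 20%: k = 1.2/1.3 = 0.923, rate ratio 0.992.
- R = 3, b = 30%, a = 15%: k = 1.3/1.6 = 0.8125, rate ratio 0.981.
- R = 5, b = 30%, a = 10%: k = 1.4/2.2 = 0.636, rate ratio 0.964.

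So k = 0.5 needs stronger selection than any of these. Likewise, if only half of the false records were vascular, k = 0.5 would mean that glitazone users had none of them.

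**4. Effect on the test.** With 144 exposed events and 720/RR comparator events (equal follow-up assumed), SE(log RR) = √(1/144 + RR/720). The chance of a significant protective result is Φ(−ln RR/SE − 1.96), which is 2.5% at RR = 1.

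- RR 0.975: SE 0.091; 0.0253/0.091 = 0.28 standard errors; chance about 4.6%.
- RR 0.95: SE 0.091; 0.0513/0.091 = 0.56 standard errors; chance about 8%.
- RR 0.90 (floor): SE 0.0905; 0.1054/0.0905 = 1.16 standard errors; chance about 21%.

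**5. Against the 10% retention rule.** Full correction from 0.975 to 1 changes the estimate by 2.6% (1/0.975 = 1.026), and from 0.95 by 5.3% (1/0.95 = 1.053). Neither reaches 10%, so the stepwise rule would drop a vascular covariate even if it were collected and removed all of this bias.

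**6. If the PPV is lower here.** With f = 0.20 (assumed), k = 0.5 gives 0.80 + 0.10 = 0.90. A rate ratio of 0.75 needs f of at least 0.25, and at f = 0.25 it needs k = 0.

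**The case against.** A reader might infer that the Protocol contradicts itself by denying that risk factors drive glitazone choice while reporting that cardiovascular concerns did. The text does not support that. The factors in the Limitations sentence are known PD risk factors, and vascular disease is not among the examples given. The prescribing passage reports the suspension of one drug. It does not say that prescribers selected patients by vascular history, and it attributes the decline in pioglitazone to bladder cancer. Exposure is fixed at the index date, so a later suspension does not by itself change who entered as exposed.

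Nor does the Protocol claim that misclassification must be non-differential or can only pull towards the null. Its wording is that this is likely and expected.

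The direction is also open. Glitazones were at first mostly second-line combination treatment, so any remaining difference in disease stage could put more vascular disease among users. At k = 1.25 the same formula gives 1.025, the opposite direction.

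Existing analyses help. The two-prescription outcome targets false records directly, and the separate drug analyses could show a pattern confined to rosiglitazone.

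All of this stands and limits the point. It does not close the gap. The two-prescription definition is a sensitivity analysis only, and the documents do not say how many wrongly labelled patients would still meet it. The drug-specific analyses may reveal a problem but do not adjust for it. Calcium channel blocker use is at most a partial proxy, and calendar year describes trends, not the individual patient.

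**Conclusion.** The omission is real; the bias is conditional and small. If vascular patients were less often started on glitazones, and if uncoded vascular parkinsonism is among the false PD records, the rate ratio would read about 0.975 to 0.95 with no true effect. That assumes 90% PPV in comparators and false records a quarter to a half rarer in users. The bias is about 0.3 to 0.6 standard errors.

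It would be wrong to conclude that this could explain the 25% reduction that the Power Calculation calls meaningful. At 90% PPV the floor is 0.90. Reaching 0.75 would need a PPV of 75% or lower in this cohort. The documents give neither a PPV by exposure nor the prevalence of vascular disease, so neither the size nor the direction can be settled from them. This is a cheap improvement of minor priority.

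**What to change.** 1. Add cardiovascular and cerebrovascular disease recorded before the index date, including stroke and heart failure, to the list in Exposures, Outcomes and Covariates.
2. Force it into the fully adjusted sensitivity model, without subjecting it to the 10% rule.
3. Repeat the primary comparison, as a sensitivity analysis, in patients without that history.
4. Qualify, without deleting, the Limitations statement on non-differential misclassification: say that it would fail if vascular disease influenced glitazone choice, and point to the analyses that examine this.

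The cost is one more code list, a few more parameters, and fewer events in the restricted analysis, which will be less precise.
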